## Abstract

**Objectives:**

Compulsory mental health care includes compulsory hospitalisation and outpatient commitment with medication treatment without consent. Uncertain evidence of the effects of compulsory care contributes to large geographical variations and a controversy on its use. Some argue that compulsion can rarely be justified and should be reduced to an absolute minimum, while others claim compulsion can more frequently be justified. The limited evidence base has contributed to variations in care that raise issues about the quality/appropriateness of care as well as ethical concerns. To address the question whether compulsory mental health care results in superior, worse or equivalent outcomes for patients, this project will utilise registry‐based longitudinal data to examine the effect of compulsory inpatient and outpatient care on multiple outcomes, including suicide and overall mortality; emergency care/injuries; crime and victimisation; and participation in the labour force and welfare dependency.

**Methods:**

By using the natural variation in health providers' preference for compulsory care as a source of quasi‐randomisation we will estimate causal effects of compulsory care on short‐ and long‐term trajectories.

**Conclusions:**

This project will provide valuable insights for service providers and policy makers in facilitating high quality clinical care pathways for a high risk population group.

AbbreviationsADHDAttention Deficit Hyperactivity DisorderCPRThe Central Population RegisterCRPDConvention on the Rights of Persons with DisabilitiesIVInstrumental VariableNPRThe Norwegian Patient RegisterOCOutpatient CommitmentRCTRandomised Controlled TrialSMISevere Mental IllnessWPWork Package

## INTRODUCTION

1

In all mental health care systems, there are limits on what is known about beneficial outcomes of different care pathways; but clinical decisions must nevertheless be made, leading to practice variations. Since this variation is typically unknown to service users, it can enable quasi‐experimental designs, valuable in a context in which Randomised Controlled Trials (RCT) are difficult, or even impossible, to conduct. This protocol is part of the project “Controversies in Psychiatry” (Mykletun et al., 2021), whose main aim is to use clinical practice variation observed in Norwegian national registries to obtain knowledge on key questions that for practical, legal, and ethical reasons are hard to answer through RCTs. The first controversy project investigated Attention Deficit Hyperactivity Disorder (ADHD) (Mykletun et al., 2021); this project highlights controversies surrounding compulsory inpatient and outpatient mental health care, including administration of medication without consent.

Insufficient high‐quality evidence on the efficacy and effectiveness of healthcare pathways creates clinical uncertainty about trade‐offs between benefits and harms for patients, and for the healthcare system and larger society. This is one reason why controversies are common in mental health care. One such controversy concerns compulsory care in hospital and community settings. Many patients experience compulsion as harmful (Nyttingnes, 2018), and report few benefits (Katsakou and Priebe, 2007). Governments (Sosial‐og Helsedirektoratet, 2006), user organisations (The National Coalition of Mental, 2015), and professionals, including the World Psychiatric Association (Herrman et al., 2022), have requested a reduction of compulsory mental health care. There are also calls for alternatives to coercion (Gooding, 2021), emphasising co‐developed options, supported decision‐making and increased user‐participation, particularly following the United Nations' Convention on the Rights of Persons with Disabilities (CRPD) (UN General Assembly, 2007). Meanwhile, mental health services are often criticised for failing to protect citizens and for not using sufficient coercion, following what remain rare acts of violence by people with severe mental illnesses (SMI) (Honningsøy & Radøy,  2021), as well as post‐discharge suicide (Moland & Zondag,  2014).

In Norway, psychiatric inpatient bed numbers have been reduced over decades with more mental health service users receiving community‐based support (Lilleeng et al., 2014), a development also seen internationally (World Health Organization, 2022). This includes compulsory community services, such as Outpatient Commitment (OC), which uses legal instruments to compel people to receive outpatient services.

### The purpose of compulsory care

1.1

The purpose of compulsory mental health care is to reduce the short‐term risk of suicide or self‐harm and reduce the risk that the person will be a victim or perpetrator of violence or acts that violate others' life, health, or freedom. In the long term, mental health care, including compulsion, is expected to facilitate recovery and prevent relapse. Improved outcomes can potentially impact beyond health and risks of harm, to influence educational attainment; employment and welfare reliance; relationships and childcare; and criminal justice involvement.

The relationship between inpatient and outpatient compulsory care remains unclear. As both are imposed on patients without their consent, it may be worthwhile to examine these practices together.

## RISK OF VIOLENCE AMONG PERSONS WITH SMI

2

When violent acts are committed by individuals with a history of mental illness, the media often highlights these incidents, leading to public debates that often blame clinicians and the healthcare system for failing to provide compulsory mental health care. These discussions generally overlook the complexity involved in deciding when to use compulsory mental health care and make assumptions about its effectiveness in preventing such incidents. The risk of violence (Dack et al., 2013) or suicide (Inskip et al., 1998) among those with SMI remains low, making risk assessment difficult, as well as producing false positives who may suffer unnecessarily from the detrimental impacts of compulsory care (Palmstierna, 1999; Rosen, 1954). Moreover, individuals with SMI are more likely to be victims of violent crime than perpetrators (Latalova et al., 2014).

### Existing evidence for effectiveness of inpatient and outpatient compulsory care

2.1

Norwegian legislation enabling compulsory mental health care (Psykisk helsevernloven med kommentarer, 2022) presupposes that compulsory care is effective, by using words such as *necessary*, which implies that the situation is expected to improve from compulsory care, compared to the counterfactual scenario without it. There is, however, limited evidence to support this assumption in relation to many outcomes, including the prevention of suicide (Zalsman et al., 2016). A recent study from Norway found no worse outcomes for people with SMI residing in areas with little use of compulsory mental health care, compared to areas with frequent use (Nyttingnes et al., 2023). A Cochrane review (Kisely et al., 2017) identified three RCTs on OC, one in England (Burns et al., 2013) and two in the United States (Steadman et al., 2001; Swartz et al., 2001). They all failed to find a difference between OC and standard “voluntary” care in relation to service use, social functioning, mental state, or life quality. OC recipients were, however, less likely to be crime victims. The Cochrane review concluded these trials were of low to medium quality and called for higher quality research. Longer term analysis of the English OC trial indicated no overall cost difference between the OC group and a voluntary treatment comparator group even from a societal perspective, with no difference in health or capability‐related life quality (Simon et al., 2021). Long term follow up similarly found no association between OC and improved social functioning 4 years later (Vergunst et al., 2017).

Another review of 60 studies concluded that the evidence is sufficiently strong to infer causally that OC does not prevent relapse or reduce hospital admission (Kisely et al., 2007). In contrast, a review of 39 studies (Segal, 2022) argues OC is associated with reduced all‐cause‐mortality. Beyond the few RCTs implemented, the observational studies conducted to date are susceptible to bias and confounding. Importantly, no RCTs have investigated the effectiveness of compulsory hospitalisation.

### The Controversy of Compulsory Care's Effectiveness

2.2

The controversy which this project protocol addresses is therefore, first, whether compulsory care^1^ results in reduced levels of mortality, suicides, and serious crime; and secondly, whether compulsory care has positive effects on outcomes such as self‐harm episodes, injuries, unemployment, and welfare reliance among people at high risk of compulsory care.

### Why RCTs are not likely to resolve the controversy

2.3

Conducting RCTs to investigate the effectiveness of compulsory care is challenging due to practical, legal, and ethical considerations. Double‐blinding care status is impossible, leading to bias risks. Strongly opinionated clinicians can hinder clinical equipoise. For financial and practical reasons, RCTs require a short time frame, making them unsuitable for answering questions related to long‐term outcomes over years. Even if these practical constraints could be mitigated, many ethics committee would not approve randomising people who meet legal criteria for compulsion to voluntary status; the English RCT on OC was required to provide a detailed legal opinion prior to approval (Dawson et al., 2011).

Some commentators argue that RCTs may be suboptimal for evaluating the effectiveness of complex interventions such as OC, which operate in open systems involving social actors (Duncan et al., 2020; Mustafa, 2017; O’Reilly and Vingilis, 2018).

Consequently, it remains unclear whether compulsory mental health care is beneficial, either at the individual or societal level, and whether outcomes expected by legislators are actually delivered. This uncertainty, coupled with differing clinician opinions, provides room for considerable practice variation.

### Variations in clinical judgement

2.4

As noted, debate has been ongoing for decades regarding compulsory mental health care. While some argue for reduction (Cratsley et al., 2021; Gooding, 2021), and even abolition of coercion in mental health care (Council of Europe Committee on Social Affairs, 2019; Zinkler and vonPeter, 2019), others believe the focus on autonomy and self‐determination has gone too far, risking inadequate care for patients and negative impacts on their well‐being, and increase risk of harm to others (Freeman et al., 2015). This has led to a spectrum of opinions among clinicians (Aasland et al., 2018; Husum et al., 2017), ranging from those who believe that compulsion can rarely, if ever, be justified to those who believe it can be justified in a substantial proportion of clinical contexts. Figure 1 illustrates this continuum of clinical views, underpinned by arguments to support each pole.

**FIGURE 1 mpr1980-fig-0001:**
[figure not shown]
Clinician preference for or against compulsion.

In clinical practice, there is likely to be greater agreement among clinicians that patients with mild symptoms and low risk should not be involuntarily admitted or subject to OC, while those with severe symptoms and high risks may require compulsory treatment (Figure 2). Consequently, the controversy primarily surrounds patients whose symptom levels and risks fall between these two extremes, who are most likely to experience variations in clinical practice dependent on clinician and system preferences. People in this *‘grey zone’* are thus more likely to be managed differently by different clinicians, or in different health systems, producing considerable variation in levels of compulsory care.

**FIGURE 2 mpr1980-fig-0002:**
[figure not shown]
Theoretical illustration of the controversy on the use of compulsory mental health care for people with severe mental illness.

### Geographical variation in compulsory mental health care: A source of concern and a toolbox for causal inference

2.5

Geographical variation in health services is more apparent in conditions where clinicians disagree about *‘right care’* (Wennberg, 2010). It is therefore unsurprising that geographical variation in compulsory hospitalisation is observed in all countries with available data: Belgium (Gedwongen verblijven in PZ en, 2021); Denmark (Engberg, 1991); England (Keown et al., 2016); Finland (The Finnish Institute for Health and Welfare, 2022); France (Gandré et al., 2018); Germany (Brieger et al., 2014); Ireland (Daly and Craig, 2021); Italy (Di Cesare et al., 2017); New Zealand (O’Brien et al., 2012); The Netherlands (Broer et al., 2020); South Korea (Hwang et al., 2020); Sweden (Statistikdatabaser, 2021); Switzerland (Schuler et al., 2018); and the United States of America (Lee and Cohen, 2021). Mental health services are expected to be of similar quality within most of these countries, and quality of care is not presumed to depend on area of residence.

Norway has a universal health care system where all residents are entitled to equal access to mental health care, and there is no separate private mental health sector. Still, after controlling for age and gender of residents, the average number of compulsorily hospitalised patients per person in the population in 2014–2018 was more than three times higher in the highest‐ranked area compared to the lowest (Hofstad et al., 2021), as illustrated on the right panel of Figure 3. Measured as the average number of days of compulsory hospitalisation per capita, the variation was more than eightfold. Compared to other European countries (Sheridan Rains et al., 2019), the average rate of compulsorily hospitalised patients in Norway is relatively high, as seen in the left panel of Figure 3.

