**FIGURE 3 mpr1980-fig-0003:**
[figure not shown]
Geographical variation in compulsory hospitalised patients in Europe and Norway. Average rates per 100.000 inhabitant. Map based on data from (Hofstad et al., 2021; Sheridan Rains et al., 2019).

There are likely many factors related to the services and their patient populations, that influence the varying rates of compulsory admission. Characteristics of service providers might include bed capacity and duration of hospitalisations (Bale et al., 2021); clinicians' evaluation of decision‐making capacity (Høyer et al., 2022); different attitudes to coercion, which has been shown to vary between professions (Aasland et al., 2018); varying interpretations of legal criteria (Feiring and Ugstad, 2014); availability of systematic family involvement and support for people with SMI (Hestmark et al., 2021); other local experience‐based practises, including quality of voluntary care, which can impact on whether compulsory care is considered necessary (Sharpe, 1997); or other individual differences in clinical decision‐making (Bagby et al., 1991). Variation related to case‐mix might include differing characteristics among the population‐at‐risk of compulsory care, such as age, gender, ethnicity, employment status, comorbidity and previous history of compulsion (Barnett et al., 2019; Walker et al., 2019).

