### WP2: Short and long‐term causal effects of compulsory inpatient and outpatient mental health care, including administration of medication without consent

3.2

The main objective of WP2 is to estimate the causal effect of compulsory mental health care on health and social functioning outcomes for people with SMI, potentially including long term costs to the public purse and society associated with these differences. We will use variation in clinical practice among catchment areas as IV to estimate the causal effect of compulsory care on multiple outcomes (see Figure 5). The primary analyses will be restricted to (a) people with SMI; and (b) people who are referred to compulsory inpatient mental health care.

We expect that patients on the margin of compulsory care after discharge will be treated differently depending on whether they live in areas with higher or lower tendency to use OC. Since OC is most often used to ensure medication compliance (Riley et al., 2019) and almost all people on OC receive antipsychotic treatment (Barkhuizen et al., 2020; Riley et al., 2019; Rugkåsa et al., 2015), we will use provider preference for use of OC as a proxy to measure the effect of administration of medication without consent. This WP will also test assumptions that must be fulfiled for IV‐estimates to credibly reflect causal relationships (Widding‐Havneraas et al., 2021).

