### Assumptions of provider‐preference instrumental variables

5.2

First, the *relevance criterion* implies that the instrument must be correlated with the treatment variable. We intend to generate IVs at the regional provider level of catchment area to Community Mental Health Centres (Ruud and Friis, 2021). Stable geographical variations in compulsory hospitalisation between catchment areas have been documented, and more than 80% of variation in ranked rates of compulsory hospitalisation per population could be predicted by the area rankings for the previous year, while 50%–75% of variation in inpatient rates could be predicted this way (Hofstad et al., 2021), suggesting that provider preference for compulsory care can be a strong instrument (Hernán and Robins, 2020).

Second, the *exclusion restriction assumption* implies the instrument should only impact the outcome through treatment. This means that service providers' preferences for using compulsory mental health care in an area should impact whether involuntary care is initiated, while being uncorrelated with outcomes through other paths. We will use a *negative control population* to test this assumption (Lipsitch et al., 2010); since provider preference should have no impact on those who were not in contact with mental health services, the impact of the instrument on the outcome should be zero in the control cohort.

Theoretically, the instrument will control for unobserved and observed characteristics of individuals that can affect the outcome. However, instrument‐outcome confounders can still bias estimates, in which case the instrument would not be equivalent to “as‐good‐as‐random assignment” (Garabedian et al., 2014). So the third *assumption of no confounding* requires that there are no unmeasured common causes of the instrument and the outcome. This will be tested indirectly through balance tests of baseline covariates (Brookhart and Schneeweiss, 2007).

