The fourth assumption of *monotonicity* ensures that the estimand can be interpreted as the Local Average Treatment Effect (LATE). Individuals who clearly fill criteria for compulsory care are assumed to be subject to compulsion in all areas, while persons where compulsory hospitalisation is clearly not indicated are not subject to compulsion anywhere. Consequently, the estimand represents the effect of compulsory care for people with SMI at the margin/in the grey zone of compulsory care; individuals who are expected to be treated differently if they live in areas with a high versus a low use of compulsory care (See Figure 2). By design, we know that all people who are assigned to the treatment (compulsory care), will receive it, thereby ensuring no ‘*defiers’*.

Subject‐matter knowledge, required for all but the first assumption, will be provided by project group members, as well as service‐users and providers. Topics meriting investigation include whether the variation is random or remains stable over time. Are there differences in case mix, with different prevalence of SMI between areas? Is there risk of selection bias, where service users residing in low‐compulsion areas, but require compulsory hospitalisation, are transferred to areas that use more compulsion?

In general, people are unaware whether rates of compulsory mental health care in their catchment area are high or low compared to the country average. Given the retrospective baseline, the quasi‐experimental framework is similar to a double‐blinded experiment where neither service users nor providers could identify the treatment. While some clinicians may have recognised that the use of compulsory care tended to be higher or lower within their area, they were unaware that they partook in a natural experiment. There is also little reason to expect that people self‐selected to areas based on compulsory hospitalisation rates, thereby reducing the risk of selection bias.

Even if the exclusion restriction assumption is violated, the ‘*reduced form’* can provide an unbiased estimate of the effect of the instrument on the outcome (Chernozhukov and Hansen, 2008), and will answer whether a higher or lower propensity for compulsory care results in superior, worse or similar outcomes for patients.

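### The exclusion restriction covers only the start of compulsion, but the protocol's own figures imply that duration also differs between areas, so an initiation-scaled LATE may be biased in an unknown direction

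*Protocol article*

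**What the plan says.** All references are to the protocol article.

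- **Exclusion restriction (section 5.2).** Preferences "should impact whether involuntary care is initiated, while being uncorrelated with outcomes through other paths". Duration is not mentioned there.
- **Estimand (section 5.2).** The result is read as a LATE for grey-zone patients. At one end, "Individuals who clearly fill criteria for compulsory care are assumed to be subject to compulsion in all areas"; at the other, some patients are compelled nowhere. The absence of defiers is argued from everyone assigned to compulsory care receiving it. This is the language of a yes/no treatment, although no sentence formally fixes a binary variable.
- **Variation (section 2.5).** Compulsorily hospitalised patients per inhabitant, controlled for age and gender, "was more than three times higher in the" top-ranked area than in the bottom one. Then: "Measured as the average number of days of compulsory hospitalisation per capita, the variation was more than eightfold".
- **Duration as a provider feature (text after Figure 3).** "Characteristics of service providers might include bed capacity and duration of hospitalisations", in a list of factors that may influence compulsory admission rates.
- **Planned checks (section 5.2).** For exclusion, a population without contact with mental health services, in which "the impact of the instrument on the outcome should be zero in the control cohort". For confounding, balance of baseline covariates.
- **Population (section 3.2, WP2).** "The primary analyses will be restricted to (a) people with SMI; and (b) people who are referred to compulsory inpatient mental health care".
- **Fallback (section 5.2).** The reduced form, if the exclusion restriction fails.

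**The concern.** An instrument scaled by initiation attributes the whole outcome difference between areas to patients whose initiation was changed. That is valid only if provider preference does nothing to the patients compelled everywhere. The protocol assumes that such patients exist, names duration among provider characteristics, and reports figures under which duration cannot be the same in all areas. The legend to Figure 6 adds that compulsion is reviewed repeatedly and that discharge can be decided at any time. A preference for compulsion could therefore plausibly act on continuation as well as on entry.

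If it does, the effect of longer compulsion in always-compelled patients enters the numerator while the denominator counts initiations only. At stake is what the headline causal estimate of WP2 can be said to show. The problem could matter most in the referred population, which plausibly contains many patients who would be compelled anywhere.

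**Working it through.** **Inputs.** From section 2.5: ratio of compelled patients per capita R_P > 3 and ratio of compulsory days per capita R_D > 8, highest against lowest area. Neither has a stated upper limit. I take R_D = 8 and, as an assumption, R_P from 3 to 4, with 5 as a further case. Both ratios come from a cited source and cannot be rebuilt from the document. The document does not give the correlation between an area's initiation rate and its days per compelled patient, or the sign of any effect per day.

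**Step 1: how far duration must differ.** For each area, days per capita D = P × L, where P is compelled patients per capita and L is days per compelled patient. For the two areas at the extremes of D, the ratio of L equals R_D divided by their ratio of P, and that ratio of P cannot exceed R_P. Hence max/min L ≥ R_D / R_P, even if different areas are extreme on the two measures.

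- R_P = 3: 8/3 = 2.67
- R_P = 3.5: 8/3.5 = 2.29
- R_P = 4: 8/4 = 2.00
- R_P = 5: 8/5 = 1.60

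**Step 2: what this does to the LATE.** Let the effect in a compelled patient be a + bL. For a low-initiation area (P_0, L_0) and a high-initiation area (P_1, L_1), the initiation-scaled estimate is

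[P_1(a + bL_1) − P_0(a + bL_0)] / (P_1 − P_0) = (a + bL_1) + b(L_1 − L_0) × P_0 / (P_1 − P_0).

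The first term is the effect in grey-zone patients, who are compelled only in the high area and so have its stay. The second term is the bias. It comes from patients compelled in both areas and vanishes only if L_1 = L_0 or b = 0. Its sign follows b(L_1 − L_0).

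**Step 3: illustrations that fit the stated ratios.** P and L are in units of the lowest area; a = 0 and b = 1 unless stated.

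- *Duration unrelated to initiation* (short and long stays equally common at both levels of P). R_P = 3: estimate 1.83 against mean stay (1 + 2.67)/2 = 1.83. R_P = 4: 1.50 against 1.50. No bias.
- *Duration rises with initiation, same direction of effect.* R_P = 3: (8 − 1)/(3 − 1) = 3.50 against 2.67, or 1.31-fold. R_P = 4: (8 − 1)/(4 − 1) = 2.33 against 2.00, or 1.17-fold. Inflated.
- *Duration rises with initiation, days act against initiation* (a = −1, b = 0.2). R_P = 3: (−1.4 + 0.8)/2 = −0.30 against −0.47. R_P = 4: (−2.4 + 0.8)/3 = −0.53 against −0.60. Attenuated.
- *Duration falls with initiation* (three areas with P = 1 and L = 1, 2.6, 2.6; three with P = 3.2 and L = 2.6, 1, 1; R_D = 3.2 × 2.6 = 8.32). Mean L is 6.2/3 = 2.07 in the low areas and 4.6/3 = 1.53 in the high areas. Estimate (3.2 × 1.533 − 2.067)/2.2 = 1.29, against 1.53 in the high areas and 1.80 overall. Attenuated.

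**Step 4: would the planned checks see it?** People without contact with services have no compulsory days, so the expected null in that cohort holds whether or not preference moves duration. Baseline balance tests look at covariates fixed before compulsion starts. Neither is informative about this path.

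**The case against.** **Direction.** A reader might infer that the LATE is inflated, because days vary more than patients. The document does not support that. It gives two separate max/min ratios, does not say that the same areas are extreme on both, and says nothing about the sign of an effect per day. The same ratios fit no bias, inflation and attenuation. This objection stands in full.

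**The 2- to 2.7-fold figure.** It is a ratio between extreme areas, not the size of a bias. It rests on reading the patient ratio as 3 to 4. It is per general population, whereas WP2 is restricted to people with SMI or referred to compulsory inpatient care. Age and gender control is stated for patients but not clearly for days. Days per patient can include repeat stays or reflect case mix, so the figure does not prove that providers lengthen anyone's stay. All of this stands: the figure makes a duration path possible but does not measure it.

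**Stability over time.** A reader might also infer that a stable preference adds later compulsory episodes in the same patients, because "more than 80% of variation in ranked rates of compulsory hospitalisation per population could be predicted by the area rankings for the previous year". That statement concerns area ranks and supports relevance only. Section 3 lists later compulsion among the outcomes, so episodes that follow from the first one belong to its total effect.

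**Left to the analysis plan, or already handled.** The exposure is not formally fixed as binary, and its definition is commonly left to an analysis plan, which is not shown here. The article also commits to testing IV assumptions, offers other models if doubt remains (section 4.1), and keeps the reduced form, which the scaling problem does not touch. This stands in part. The assumption as written still names initiation only, the checks named for it cannot see duration, and a fallback helps only if the violation is noticed.

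**Conclusion.** The point holds in conditional form. The exclusion restriction is worded for initiation alone, while the protocol's own ratios imply that days per compelled patient differ between some areas by at least about 2.0- to 2.7-fold (patient ratio 3 to 4; 1.6-fold at 5). If provider preference is part of the reason, an initiation-scaled LATE mixes the effect of being compelled with the effect of longer compulsion in patients who would be compelled anywhere. Neither named check would show it.

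The bias has unknown size and direction. In the illustrations above, all consistent with the stated ratios, it runs from attenuation through none to about 1.2- to 1.3-fold inflation. Those values depend on assumed correlations and effects and are not estimates for this study. The reduced form remains interpretable throughout. The point is worth acting on because it changes what the LATE can be claimed to show and the remedy is cheap.

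**What to change.** In WP2, use the patient register's in/out dates, judicial reason for stay, involuntary admission and outpatient commitment variables, all already listed in Table A1:

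1. Report the association of the instrument with compulsory days among compelled patients, as an added exclusion check. Read it with care: high-preference areas compel more grey-zone patients, so the mix of compelled patients shifts with the instrument. Show it with adjustment for baseline case mix, and do not take a null result as proof.
2. Add, as a secondary analysis, an IV estimate per fixed number of compulsory days in a fixed window, for inpatient care and outpatient commitment separately. State the linearity assumption and how death within the window is handled.
3. If step 1 shows an association, label the initiation-scaled LATE as the effect of a compulsion package that includes duration, and present it beside the reduced form.

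I would not make cumulative days the primary treatment. Days are cut short by death, and mortality and suicide are lead outcomes. Later days overlap with compulsory rehospitalisation as an outcome. Any effect of being compelled as such would become the new excluded path.

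The cost is one derived variable, a modest amount of analysis and a more cautious reading of the LATE. No new data are needed.
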